### *Observation*

Multiple observation sessions may be arranged at hospital settings, if interviews do not provide sufficient insights. The aim of this observation might help to explore more insights from real-life experiences for introduction of BCPAP, service provider, child and caregivers' responses to the treatment of BCPAP. For this, the study team may spend time in the ward for observing and talking (informal conversation) to the caregivers and service providers (health worker, nurses or physicians) when they will be closely involved in providing treatment and child caring respectively. More specifically the observation may be held to understand:

- Ward environment (e.g., availability of bed in pediatric ward, attitude of physicians/consultants, nurses, health workers towards patients and their caregivers, cleanliness, electricity and other facilities, etc)
- Treatment practices (e.g., follow up visits, medication, interaction between patients' caregiver and hospital staff, patients' response to BCPAP, availability of oxygen support, the process of preparing the BCPAP circuit and functioning (capture if there is any difficulty, etc.)
- Treatment outcomes (e.g., well and discharged; diagnosed as a chronic illness and discharged with medication; died at the hospital).

Interviews, FGDs and observation will be conducted using flexible semi-structured guidelines (see annex-11) and equal in numbers in each of the study sites. As is the nature of qualitative study, guidelines might be revised for Stage III data collection based on experience and study findings of Stages I and II. Study participants will be selected purposively based on the characteristics of patients and caregivers, experience and knowledge of participants about the study subject. The data collection team will be males and females with a master's degree in Anthropology or Sociology as well as few years experience in collecting qualitative data. They will be trained by qualified Anthropologist.

For qualitative assessments, following number of participants will be interviewed for primary data collection in different episodes of quantitative assessment:

| Qualitative Assessment    | Data collection techniques | Number of participants |
|---------------------------|----------------------------|------------------------|
|                           | Key Informant Interview    | 8-10                   |
|                           | In-depth Interview         | 10-15                  |
|                           | Focus Group Discussion     | 20-30                  |
|                           | Observation                |                        |
| Total participants |                            | 38-55                  |

**Data Analysis:** Descriptive analysis of level of feasibility and acceptability will be performed by calculating the proportion of challenges such as lack of availability of oxygen, intravenous cannula, lack of assessment of vital sign etc.

For qualitative part: According to the nature of qualitative assessment, analysis will begin with the first field activities (in-depth interview, observation and FGD) and lead to improvement as the study proceeds. Field notes and dairy will be reviewed by the research team on a regular basis (initially, daily). For analyzing data, the processes will follow a sequence of inter-related steps that includes reading, coding, displaying, reducing, and interpreting. At first, transcripts will be carefully read, and then coding of data will begin. Reading and coding will initiate while data are being collected. The data-display and reduction process will be conducted once all data have been collected. Even during data display and reduction, the investigators will loop back through earlier steps to refine codes, re-read texts, and revise some aspects of analysis. After reading, re-reading, and coding the text, the main themes will be finalized. However, the complex issues will be presented in some verbatim forms. Each theme will then be examined separately and fully within the available data.

### **Stage III. Testing effectiveness of locally constructed bubble CPAP in general hospitals.**

**Study Design:** During this Stage, a two arm cluster randomized clinical implementation trial will be undertaken at six district hospitals per arm. The study arms are:

- i) Intervention arm (young children with severe pneumonia and hypoxemia treated by bubble CPAP) and
- ii) Control arm (children treated with the WHO standard low-flow oxygen therapy up to the maximum flow rates for nasal cannula therapy without humidification)

### **Study setting**

The study will be done in 12 district hospitals (6 in each arm) from all regions throughout Ethiopia. District hospitals will be selected randomly from all regions throughout the country. (Annex 13)

**Inclusion criteria & Exclusion criteria** - Same as Stage I

## Primary outcome

The primary outcome of the study is treatment failure. According to this protocol treatment failure will be declared if any of the following criteria is met:

- B. Presence of severe hypoxemia ( $\text{SpO}_2 < 85\%$ ) at any time after at least one hour of intervention plus respiratory distress when the child is receiving BCPAP/LF  
OR,
- C. If the patient developed the indication of mechanical ventilation when the child is receiving BCPAP/LF  
OR,
- D. If the patient died during hospitalization or within 72 hours of left against medical advice (LAMA)  
OR,
- E. If the patient left against medical advice (LAMA) when the patient is still on study intervention

## Secondary Outcomes

- Death during hospitalization
- Deaths during hospitalization plus within 72 hours of LAMA
- Pneumothorax
- Aspiration pneumonia
- Length of hospital stay
- Incidence of nasal trauma, gastric distention, shock and air leaks
- Duration of bCPAP

## Sample and sampling procedure:

In this trial, our recruitment goals are approximately a total of 1240 children (620 children each for LF oxygen and bubble CPAP therapy) for a power of 80% and effect size of 50% (reduction of treatment failure, primary outcome of the study, from chart analysis 10% treatment failure in 2019 in comparison facilities) for 12 clusters (103-104 patients in each cluster), adjusted for a intra-cluster correlation coefficient (ICC) level of 0.003 required for cluster randomization. For the calculation of sample size we have used following formula:

Where,  $DF$ , Design effect =  $1 + \delta(m-1)$  [here  $DF=1.52$ ],

$n_1$  = Required minimum sample size per arm,  $\delta$  = the inter cluster correlation,  $m$  = the number of patients in each cluster [103.3 in this study],

$P_1$  = the percentage of treatment failure of children with pneumonia receiving standard treatment (low flow) = 10%,

$P_2$  = the expected percentage of treatment failure of children with pneumonia who will receive intervention (bubble CPAP) = 5% [we have observed 5% treatment failure in two district hospitals during the stage II of our study which correspond 50% effect size],  $Z_\alpha$  = the z-score value [here,  $Z_\alpha = 1.96$  at 5% level of significance],  $Z_\beta$  = the z-score value [here,  $Z_\beta = 0.84$  at 80% power]. We are intending to enroll same number of children (103-104) having our eligibility criteria from each hospital (cluster) irrespective of receiving intervention (bubble CPAP) or standard treatment (low flow).

As a run-in period we will enroll 2 participants in each hospital which will be excluded from final analysis.

**Data collection:** Data will be collected by individual patient assessment through systematic observations using a structured questionnaire. Socio-demographic and different clinical data will be collected. The questionnaire will include the baseline characteristics, intervention and outcome data. All study data will be collected by dedicated study personal at sites.

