|                                        | 
pneumonia and hypoxemia
 
 
- To record adverse events (pneumothorax, abdominal distension, nasal trauma, aspiration pneumonia) encountered.
 
                                                                                                                                                                                                                                                                                                                                                    |
| Number of Participants/Patients | 
Stage I-30 children in each tertiary hospital
 
Stage II- 20 children in each general hospital (2 general hospitals)
 
Stage III-620 children in each arm of the study (6 hospitals in each arm)
                                                                                                                                                                                                                                                                                                                                    |
| Main Inclusion Criteria         | 
 
- Age between 1 month and 59 months
 
-Meet WHO clinical criteria for severe pneumonia with hypoxemia
 
-Hypoxemia (Oxygen saturation <90% in room air)
 
-Parent/guardian gives informed consent to participate in the study
 
                                                                                                                                                                                                                                              |
| Statistical Analysis            | 
A descriptive analysis of data of stages I and II will be performed to assess the level of feasibility and acceptability both at provider and patient levels
 
 
- In stage III we shall follow the principle of intention to treat (all children enrolled in the study will be included in the analysis irrespective of whether they have completed the study intervention). Primary and secondary outcomes will be analyzed using <math>\chi^2</math> or Fisher's exact tests as appropriate.
 
 |

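### The printed design effect of 1.52 contradicts the stated ICC of 0.003 and cluster size of 103.3, which give 1.31; 620 per arm fits 1.31 but falls short of 80% power at 1.52, and no allowance is made for having only 12 hospitals

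*Protocol*

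**What the plan says.** The protocol's Stage III section on sample and sampling procedure plans "a total of 1240 children (620 children each for LF oxygen and bubble CPAP therapy", "for a power of 80% and effect size of 50"%, in 12 hospitals. The Summary agrees: "Stage III-620 children in each arm of the study (6 hospitals in each arm").

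The inputs given are:

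- control failure rate: "the percentage of treatment failure of children with pneumonia receiving standard treatment (low flow) = 10"%;
- bubble CPAP failure rate: "the expected percentage of treatment failure of children with pneumonia who will receive intervention (bubble CPAP) = 5"%;
- a z-value of 1.96 at the 5% level and of 0.84 for 80% power;
- clustering: the size is "adjusted for a intra-cluster correlation coefficient (ICC) level of 0.003 required for cluster randomization";
- cluster size: "the number of patients in each cluster [103.3 in this study"].

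The design effect is defined as one plus the ICC times (m − 1), and its value is printed as 1.52. The equation for the per-arm size does not appear in the text available for this review, so whether it carried a continuity correction cannot be seen.

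**The concern.** The ICC, the cluster size and the design effect are tied by a formula that the protocol prints, and the three values do not satisfy it. Of the three, the design effect is the one that multiplies the individually randomised sample size, so an error there bears directly on the claim of 80% power for the primary outcome.

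Two consequences follow. First, the protocol supports two different ICCs, 0.003 as written and about 0.005 as implied by the design effect, and 620 per arm is enough for only one of them. Second, z-values of 1.96 and 0.84 treat the between-hospital variance as known, although it would be estimated from six hospitals per arm. The power statement governs how a null result would be read. If it is too favourable, a non-significant result could be taken as stronger evidence against a halving of treatment failure than the design can give.

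**Working it through.** **Inputs** (all from the Stage III sample-size section): P1 = 0.10, P2 = 0.05, z-values 1.96 and 0.84, ICC = 0.003, m = 103.3 (620/6 = 103.33), six hospitals per arm, n = 620 per arm, printed design effect (DF) 1.52.

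**1. Design effect**

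- DF = 1 + ICC × (m − 1) = 1 + 0.003 × 102.3 = 1.307.
- ICC needed for 1.52: 0.52/102.3 = 0.0051. An ICC of 0.005 gives 1.51.
- Cluster size needed for 1.52 at ICC 0.003: 1 + 0.52/0.003 ≈ 174, far from 103.3.

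The printed inflation above 1 is 0.52 and the implied one is 0.31, so rounding does not explain the gap.

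**2. Reproducing 620**

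Size per arm before clustering:

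- Unpooled variance: (1.96 + 0.84)² × (0.09 + 0.0475)/0.05² = 431.2.
- Pooled variance under the null: 433.9.
- Continuity-corrected, from the pooled n: (n/4) × [1 + √(1 + 4/(n × 0.05))]² = 473.1, rounded up to 474.

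| Formula | n before clustering | × 1.307 | × 1.52 |
|---|---|---|---|
| Unpooled | 431.2 | 563.5 | 655.4 |
| Pooled | 433.9 | 567.1 | 659.6 |
| Continuity-corrected | 474 | **619.5** | 720.5 |

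The continuity-corrected size with ICC 0.003 rounds up to 620. Solving directly for six clusters per arm gives the same: 474 × (1 − 0.003)/(1 − 474 × 0.003/6) = 619.4. With DF 1.52, none of the three formulas gives 620. An arcsine-transformed size (423.3) is the smallest of the other standard variants tried, and it still gives 423.3 × 1.52 = 643.

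**3. Power at 620 per arm, on the protocol's own normal basis**

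λ = 0.05/√(0.1375 × DF/620), and power = Φ(λ − 1.96).

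- DF 1.307: λ = 2.94, power 83.6%.
- DF 1.52: λ = 2.72, power 77.7%.

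With the continuity correction, the corresponding powers are 80.1% and 73.3%.

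**4. Power with 12 hospitals**

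A comparison that respects clustering has 12 − 2 = 10 degrees of freedom for between-hospital variation. The critical value is then 2.228 instead of 1.96. The noncentral t with the same λ gives:

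- DF 1.307: 75.4%.
- DF 1.52: 69.0%.

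**5. Sensitivity to the ICC** (assumed values; the protocol gives none above 0.003)

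On the same 10-degree-of-freedom basis with m = 103.3, ICC 0.01 (DF 2.02) gives about 57% and ICC 0.02 (DF 3.05) about 41%.

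**The case against.** The strongest reply is that 1.52 is an isolated slip. The ICC is stated in words, and ICC 0.003, m = 103.3, 12 clusters, 10% against 5%, 80% power and 620 per arm all fit together under a common continuity-corrected formula. On that view only the bracketed design effect is out of line, and neither the sample size nor the number of hospitals changes. Much of this stands. A reader who tries only the uncorrected formulas might infer that 620 follows from neither design effect. The protocol does not support that inference, because 474 × 1.307 = 619.5 and the equation that would show whether a correction was used is not in the available text.

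The reply also says that 69% to 75% power is not an arithmetic error in the plan. That stands too. A reader might infer that the stated 80% is simply false, but on the protocol's z-values and ICC it is met (about 84%, or 80.1% continuity-corrected). The lower figures apply only to a t reference on 10 degrees of freedom, and the Stage III data analysis section names no such analysis. It lists χ² or Fisher's exact tests and log-binomial regression.

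Two things do not fall away. The protocol says in so many words that the design effect used here is 1.52, and with that value 620 is too few on every formula tried. And the fact that the listed tests do not mention clustering does not make normal quantiles adequate for six hospitals per arm. It leaves the power of a cluster-respecting analysis unstated.

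**Conclusion.** The contradiction is certain: the stated ICC, cluster size and formula give a design effect of 1.31, not 1.52. What it does to power depends on which figure was intended.

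- If ICC 0.003 was intended, 620 per arm stands, assuming a continuity correction was used, and only the printed design effect is wrong.
- If an ICC of about 0.005 was intended, 620 is short by roughly 35 to 100 children per arm (655 to 720 needed), and the stated 80% becomes about 78%, or 73% continuity-corrected.

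The agreement of 620 with 1.31 favours the first reading, but the protocol does not settle it. Separately, and conditional on an analysis with 10 degrees of freedom, the power for a halving from 10% to 5% is about 75% or 69%. That is a limitation of the design calculation rather than a miscalculation. All power figures assume equal cluster sizes and the protocol's two failure rates.

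**What to change.** Keep 1240 children and 12 hospitals, and amend the Stage III sample-size section as follows.

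1. Confirm the ICC that was used and state its source.
2. If it is 0.003, print the design effect as 1.31, keep 620, and name the sample-size formula together with its continuity correction.
3. If it is about 0.005, correct the ICC and restate the power at 620 per arm as below 80% (about 78% by the normal approximation, about 73% continuity-corrected).
4. In either case, report the power that six hospitals per arm deliver on 10 degrees of freedom: about 75% for ICC 0.003 or 69% for design effect 1.52.
5. Add a short sensitivity line for larger ICCs, for example 0.01 and 0.02 (about 57% and 41%), labelled as assumptions.

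The cost is protocol wording, with no extra children or hospitals. The downside is that the stated power becomes less favourable.

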### **Data quality assurance**

The study site supervisors will follow the randomization process and make sure that appropriate clinical follow up is done for the study participants and data collection tools are filled appropriately.

Supervision visit will be made to each study site every quarter by the principal investigator and the co-investigators to randomly assess the completeness of data. Moreover, by

random visit the trueness of data collection would be evaluated. Furthermore, data and safety monitoring board (DSMB) constituted by the IRB may randomly visit the study site and check any data to evaluate the integrity of data. The DSMB will also sit at least once after every 6 months to know the study progress and data procedure.

## Study setting

The study will be done in the 12 district hospitals (6 in each arm) which are part of the effectiveness study.

**Data analysis:** Quantitative data will be analyzed using STATA -14 following the principle of intention to treat. Treatment failure and/or death will be analyzed using  $\chi^2$  or Fisher's exact tests. Primary and secondary outcomes will be compared by calculating relative risks (RRs) at 95% confidence interval. Log-linear binomial regression will be applied to identify the predictors of primary and secondary outcomes after adjusting for potential confounders. Continuous variables will be analyzed using the Mann-Whitney test.

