|                                                   |                                                                                                                                                                                                                                                                                                                                                                                                                                                                                                                                                                                                                                              |
|---------------------------------------------------|----------------------------------------------------------------------------------------------------------------------------------------------------------------------------------------------------------------------------------------------------------------------------------------------------------------------------------------------------------------------------------------------------------------------------------------------------------------------------------------------------------------------------------------------------------------------------------------------------------------------------------------------|
|                                                   | 
-Continuous variables will be analyzed using the Student t-test or the Mann-Whitney test as appropriate.
 
-The primary outcome of the study is treatment failure and the secondary outcomes are death, pneumothorax, abdominal distention, nasal trauma, aspiration pneumonia.
 
-Primary and secondary outcomes will be compared by calculating relative risks (RRs) and their 95% confidence intervals.
 
- Log-linear binomial regression will be applied to adjust for covariates to evaluate the true impact of bubble CPAP in evaluating primary and secondary outcomes and to adjust for baseline differences.
 |

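### Stage III randomises 12 hospitals but its named tests treat 1240 children as independent, so on the plan's own design effects the chi-square test has a type I error of about 9–11%, not 5%

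*Protocol*

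**What the plan says.** The protocol's Stage III study design states that "a two arm cluster randomized clinical implementation trial will be undertaken at six district hospitals per arm". The hospital is therefore the unit of randomisation, with 12 in all.

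The sample-size paragraph accepts that children in one hospital are correlated. The target is "a total of 1240 children (620 children each for LF oxygen and bubble CPAP therapy"), and it is "adjusted for a intra-cluster correlation coefficient (ICC) level of 0.003 required for cluster randomization". The paragraph gives the design effect as one plus the ICC times (m − 1), takes m as "the number of patients in each cluster [103.3 in this study"], and prints the result as 1.52.

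The Stage III data analysis text in section 5.2 then sets out the comparison of treatment failure and death: chi-square "or Fisher's exact tests. Primary and secondary outcomes will be compared by calculating relative risks (RRs) at 95% confidence interval". It adds log-binomial regression with adjustment for confounders, and Mann-Whitney for continuous variables. The Statistical Analysis row of the Summary repeats this, adds the t-test, and describes the regression's role as follows: "Log-linear binomial regression will be applied to adjust for covariates to evaluate the true impact of bubble CPAP". Neither place mentions hospital as a cluster, a random effect, GEE, a cluster-robust variance, a design-effect correction or a hospital-level comparison.

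**The concern.** The design and the sample size treat the hospital as the independent unit; the analysis treats the child as the independent unit. Both cannot be right, and the randomisation settles which is.

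When whole hospitals are allocated, the difference between arms carries the hospital-to-hospital variation as well as the binomial variation between children. An ordinary chi-square or Fisher test counts only the second. It also uses a reference distribution suited to 1240 independent units, when the comparison between arms has only 12 − 2 = 10 degrees of freedom. P-values come out too small and intervals too narrow, and enrolling more children per hospital makes the understatement worse.

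At stake is the trial's main conclusion. The Rationale presents this trial as a basis for national and global policy change. With six hospitals per arm, a p-value just under 0.05 from these tests could reflect ordinary differences between hospitals.

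**Working it through.** **Inputs, all from the Stage III sample-size paragraph:** 620 children per arm; 12 hospitals; m = 103.3; ICC 0.003; printed design effect 1.52; failure rates 10% and 5%; z = 1.96 and 0.84.

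**Step 1. Design effect (DE).** The plan's formula with its own inputs gives

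DE = 1 + 0.003 × (103.3 − 1) = 1.307,

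not 1.52. The printed 1.52 would need an ICC of 0.52 / 102.3 = 0.0051. The plan thus contains two design effects, and both are carried below.

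**Step 2. Reproducing the plan's 620 per arm.**
- Two proportions, pooled variance, continuity correction: 474 per arm. 474 × 1.307 = 619.5, which rounds up to 620.
- Without the correction: 431 (unpooled) or 435 (pooled) per arm, giving 564 or 569 at DE 1.307 and 655 or 661 at DE 1.52.
- With the correction at DE 1.52: 720.

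Only the first version reaches 620, so the planned size appears to rest on 1.307.

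**Step 3. Type I error of the unclustered test.** With no treatment effect, the true variance of the difference is DE times the variance that the chi-square test assumes. Hence

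true error = 2 × (1 − Φ(1.96 / √DE)).

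| Design effect | √DE | 1.96 / √DE | True type I error | Coverage of nominal 95% CI |
|---|---|---|---|---|
| 1.307 (ICC 0.003) | 1.143 | 1.714 | 8.6% | 91.4% |
| 1.52 (as printed) | 1.233 | 1.590 | 11.2% | 88.8% |

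For the design effect alone, a correct interval is 1.14 or 1.23 times as wide. Using the t quantile on 10 df (2.228) in place of 1.96 adds a factor 2.228 / 1.96 = 1.137, for a total of about 1.30 or 1.40.

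**Step 4. Simulation check.** Beta-binomial data, six hospitals of 103–104 children per arm, the same failure rate in both arms (5%, 7.5% or 10%), 40,000 runs per setting:

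| Method | No clustering | ICC 0.003 | ICC 0.0051 (DE 1.52) |
|---|---|---|---|
| Chi-square, rejection rate | 4.9–5.2% | 8.4–8.5% | 11.1–11.5% |
| Fisher's exact, rejection rate | 3.9–4.0% | 6.7–7.2% | 9.4–9.5% |
| Unclustered RR interval, coverage | 95% | 92% | 89% |
| t-test on hospital proportions (10 df), rejection rate | 4.8–5.1% | 4.9–5.1% | 4.9–5.0% |

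**Step 5. Sensitivity to the ICC.** The protocol gives no source for 0.003. As an assumption only, at ICC 0.01 (DE 2.02) or 0.02 (DE 3.05) the formula gives a chi-square error of about 17% or 26%. The hospital-level t-test stayed at 4.7–5.1% in the simulation.

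**Step 6. Power of the valid test.** The standard error of the difference is √(DE × (0.10 × 0.90 + 0.05 × 0.95) / 620) = 0.0170 at DE 1.307 and 0.0184 at DE 1.52. A difference of 0.05 is then 2.94 or 2.72 standard errors. Referred to a non-central t on 10 df, power is about 75% or 69%. The normal approximation, which ignores the small number of hospitals, gives 83% or 77%.

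**The case against.** The best defence is that the protocol never says children are independent. It plainly knows about clustering. A relative risk or a log-binomial regression can be fitted with a cluster-robust variance, a random effect or GEE, and an analysis plan not seen here may specify that. For those two methods this is fair: the absence of a hospital term is read from the description, which speaks only of covariates, confounders and baseline differences. It does not help the chi-square, Fisher, t and Mann-Whitney tests, which are named and in their ordinary form have no place for hospital. An analysis plan that did handle clustering would contradict the protocol, so the text needs changing either way.

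Four narrower points stand and limit the size claimed:
- The range of 9–11% is for chi-square. Fisher's test gives about 7–9.5%. With 62 and 31 expected failures in the two arms (620 × 10% and 620 × 5%), chi-square is the natural choice for the primary outcome.
- The upper figure depends on the printed 1.52, which the sample size does not appear to have used. The better-supported figure is 8.6%.
- No ICC is given for death, adverse events or length of stay. The fault applies to those comparisons, but its size there is unknown, and for rare events Fisher's test would soften it.
- The errors at ICC 0.01 and 0.02 rest on values that are not in the protocol and carry no weight in the conclusion.

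**Conclusion.** The concern holds. The protocol names specific unclustered tests for the primary outcome of a trial that randomises 12 hospitals, and nothing in it reconciles the two. On the plan's own figures, the chi-square test at nominal 5% has a type I error of 8.6% (DE 1.307) or, if the printed 1.52 is right, 11.2%. Fisher's test also exceeds 5%. Nominal 95% intervals cover about 91% or 89%. These figures assume near-equal hospital sizes, as planned, and an ICC no larger than the plan's own; a larger ICC makes matters worse. The error affects the primary test, its interval and the secondary comparisons, so it must be corrected before the data are analysed.

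**What to change.** Replace the Stage III analysis text, in section 5.2 and in the Summary, with one primary method that respects the 12 hospitals. Either of these is sound:

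- **Hospital-level comparison.** A t-test on 10 df of the 12 hospital failure proportions, or of their logarithms if the relative risk is the target.
- **Child-level model with clustering.** A GEE or mixed log-binomial or modified Poisson model with hospital as the cluster, a small-sample variance correction and a t reference on 10 df. Uncorrected sandwich standard errors are too small with 12 clusters and should not be used.

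Apply the same rule to death, the adverse events, length of stay and the adjusted regression. Keep chi-square and Fisher for description only. Reconcile the design effect (1.307 or 1.52) in the same amendment, and restate power for the method chosen.

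The change costs protocol wording and a different Stata command, with no new data. The price is wider intervals and power of about 75% or 69% for the hospital-level test, against the planned 80%. That shortfall is already in the design, and the unclustered tests only conceal it.
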